#### Recruitment

Recruitment methods include collaborations with the Postpartum Support International (PSI) and with the University of California, San Francisco (UCSF) Clinical & Translational Science Institute (CTSI). These partners will disseminate study information via emails to participants and partners in their programs, with affiliate organizations and community partners using a study-specific flyer, and by social media advertising.

### Intervention and Comparator

#### Daylight

Participants who are randomly assigned to receive dCBT will be provided with complimentary access to Daylight [36]. The program uses an online therapist to guide individuals through interactive exercises and animations to facilitate the learning and implementation of 4 key CBT techniques. The four CBT techniques are cognitive (eg, identifying catastrophic thinking) and behavioral (eg, increasing physical relaxation and reducing avoidance) skills that can reduce anxiety with repeated use. At present, the Daylight app is only available in English. See Table 1 for a more detailed description of each intervention module.

Daylight is designed to be self-paced, with the app encouraging users to practice techniques both within the app and in real-life situations on a daily basis. Upon signing up, users automatically receive reminders and motivational messages via email and can choose to opt in for additional communication through text messages and push notifications to encourage daily use and intervention adherence, a prominent challenge in digital interventions [37]. Each of the 4 modules takes between 10 and 20 minutes to complete. In addition, shorter 5-minute exercises guide users through various skills (eg, progressive muscle relaxation) and are designed for repeated use over the intervention period. Weekly in-app assessments of anxiety, depressive symptoms, and sleep are also used, allowing for personalized feedback based on users’ self-reported symptoms. For example, if a user reports difficulties with sleep, they may receive prompts to engage in relaxation techniques at bedtime. Daylight provides objective metrics for engagement, including the number of modules completed, the frequency with which the app is accessed, and the time spent to complete modules. All participants in THRIVE will receive access to Daylight for 12 months after delivery (ie, until their baby is a year old).

#### Waitlist Control

The waitlist control group participants will get complimentary access to the Daylight program after completing the 10-week follow-up survey. A waitlist control condition was chosen to ensure that the entire low-income sample, a group with documented health disparities during the perinatal period [38], would have access to the intervention. Allowing access to the intervention 10 weeks following randomization allows for access to treatment in pregnancy and reduces the risk of participant dropout, which tends to increase the longer participants are asked to wait to receive treatment [39]. All participants can also continue using other pharmacological or nonpharmacological interventions (excluding CBT) for anxiety or other symptoms.

### Study Procedures and Timeline

#### Initial Screening and Orientation

Before enrolling, candidate participants will complete a 3-part screening and orientation process. First, participants will complete a screening consent form, followed by a screening questionnaire that will assess all inclusion and exclusion criteria. Second, candidate participants will verify key information submitted on the screening questionnaire via email (eg, expected due date and prenatal care provider) to minimize the risk of fraudulent screeners. Finally, candidate participants will attend a live online group orientation session where a staff member will provide an overview of the study and provide participants the opportunity to ask questions. This multistep process has maximized study engagement and retention in previous longitudinal RCTs [40].

#### Assessment Collection and Study Timeline

All participants, regardless of randomization grouping, will receive surveys that take approximately 20 minutes to complete at enrollment and at 3, 6, and 10 weeks after randomization that asks about health and well-being as well as about current experiences of anxiety, stress, depression, and sleep. As described in Table 2, demographic information collected at screening and enrollment includes information about race and ethnicity, insurance, housing stability, and food security. Pregnancy history and data about any previous preterm births, cesarean sections, or preeclampsia are collected only at enrollment. Information about pregnancy health and the diagnosis of conditions like gestational hypertension and gestational diabetes is collected across all time periods. Information about medical care and social support is also consistently collected across time periods.

**Table 2 table2:** Overview of surveys and schedule of data collection for the Transforming Health and Reducing Perinatal Anxiety through Virtual Engagement (THRIVE) phase I randomized clinical trial

Instrumentation		Time point					
Measure	Validated for use in pregnancy	Screening	Enrollment	3 weeks+/- 1 week	6 weeks+/- 1 week	10 weeks+/- 1 week	7 weeks after delivery+/- 1 week
Demographics	—^a^	✓	✓				✓
Pregnancy outcome and history	—		✓				
Pregnancy health	—	✓	✓	✓	✓	✓	✓
Care and social support	—		✓	✓	✓	✓	✓
Labor and delivery experience	—						✓
Infant health and wellbeing	—						✓
GAD-7^b^	Yes	✓		✓	✓	✓	✓
PSS-4^c^	Yes		✓	✓	✓	✓	✓
PRAS^d^	Yes		✓	✓	✓	✓	
ISI^e^	Yes		✓	✓	✓	✓	✓
PHQ-9^f^	Yes		✓	✓	✓	✓	✓

^a^Not applicable.

^b^GAD-7: Generalized Anxiety Disorder 7 Scale.

^c^PSS-4: Perceived Stress Scale 4.

^d^PRAS: Pregnancy Related Anxiety Scale.

^e^ISI: Insomnia Severity Index.

^f^PHQ-9: Patient Health Questionnaire-9.

The final survey at 6-8 weeks after the expected date of delivery will ask participants to report on symptoms of anxiety, stress, depression, and insomnia as well as their experience of labor and delivery and the health of their baby. All surveys will alert participants to missing items to reduce missing data resulting from participant error. Participants will be contacted via email, phone, or text message, according to participant preference, with reminders to complete their surveys. Following the completion of each of the 4 surveys, participants will receive a US $50 electronic gift card sent via email. See Figure 1 for a schematic representation of the RCT and the optional focus group discussions.

**Figure 1 figure1:**
[figure not shown]
Study schema for randomized controlled trial and optional focus group discussion. dCBT: digital cognitive behavioral therapy.

### Ethical Considerations

#### Overview

This study has been approved by the Western Copernicus Group (WGC) institutional review board (IRB; approval number 1364733) and registered in the Clinical Trials Registry of the National Institutes of Health National Library of Medicine (protocol number NCT06404450). The clinical protocol for THRIVE (version 1.1) was IRB-approved and has not been changed since November 14, 2023. This study protocol was guided by the SPIRIT (Standard Protocol Items: Recommendations for Interventional Trials), 2013 statement [41]; the SPIRIT checklist is available in Multimedia Appendix 1. All roles and responsibilities of study personnel and study funders are described in Multimedia Appendix 2.

#### Informed Consent and Privacy Considerations and Data Monitoring

Informed consent will be obtained from pregnant women who qualify for the study after initial screening and following participation in a scheduled orientation session. Participants will complete consent forms (see Multimedia Appendix 3) online with the capture of electronic signatures. All potential participants will be offered the opportunity to complete consent forms with the help of study staff. Information in the consent form is also reviewed at the orientation session attended by eligible participants.

Personal identifying information (eg, first and last name, date of birth, phone number, email address, and postal address) will be collected at the time of enrollment and stored separately from all other study data with linkage only by a study ID, which is only available to a small set of study personnel. Participants will be instructed to complete all research activities in a private setting. In addition, participants will be assigned unique, coded, confidential identifiers that will be used to label all data forms, data entries, and questionnaires. The key linking participant identity to their unique coded identifier will be stored on REDCap (Research Electronic Data Capture; Vanderbilt University). REDCap is a secure, HIPAA (Health Insurance Portability and Accountability Act)-compliant web-based software platform designed to support data capture for research studies, providing (1) an intuitive interface for validated data capture, (2) audit trails for tracking data manipulation, and (3) automated export procedures for seamless data downloads to common statistical packages [42]. Access to all data will be limited to the principal investigator and trained, authorized study staff. All data (recordings, transcripts, surveys, coded data) for the study are stored on encrypted servers kept behind UCSF firewalls, where access is by remote access with dual authenticated password protection. No study data is kept or accessible on local devices.

## Results

Grant funding was received in July 2023. As of March 2025, a total of 24 participants were confirmed eligible and randomized. We expect that data analysis and results will be available in May 2026.

### Primary Outcome: Anxiety Symptoms

Anxiety is self-reported using the GAD-7 [34]. The GAD-7 measures the frequency of generalized anxiety symptoms in the previous 2 weeks. Items are scored on a 4-point Likert scale (0=not at all to 3=nearly every day) and summed for a possible total score of 0-21, where higher scores indicate greater elevations in clinically significant anxiety. Cutoff points for the GAD-7 indicate that scores totaling 5-9 correspond to minimal anxiety; 10-14, to moderate anxiety; and 15-21, to severe anxiety. The GAD-7 shows strong psychometric properties, including sensitivity, specificity, and internal consistency in nonpregnant [34,43] and pregnant adults [44].

### Secondary Outcomes

#### Depressive Symptoms

Depression is self-reported using the 9-item Patient Health Questionnaire-9 (PHQ-9 [45]). The PHQ-9 measures the frequency of depressive symptoms over the past 2 weeks. Items are scored on a 4-point Likert scale (0=not at all to 3=nearly every day) and summed for a possible total score of 0-27, with higher scores indicating greater depression severity. Cutoff points for the PHQ-9 indicate that scores totaling 5-9 correspond to minimal depression; 10-14, to moderate depression; 15-19, to moderately severe depression; and 20-27, to severe depression. The PHQ-9 is the most widely used depression screening measure globally and shows convergent and criterion validity as well as good sensitivity and specificity among pregnant and postpartum samples [46].

#### Perceived Stress

Perceived stress is self-reported using the 4-item Perceived Stress Scale (PSS-4) [47]). The PSS measures the frequency of stressful thoughts and feelings over the past month. Items are scored on a 5-point Likert scale (0=never, 4=very often) and summed for a possible total score of 0-16, with higher scores indicating higher perceived stress. The PSS shows internal consistency and construct validity among several adult samples [48] as well as convergent and concurrent validity and internal consistency in pregnant people [49].

#### Pregnancy-Specific Anxiety

Pregnancy-specific anxiety is measured using the 10-item Pregnancy-Related Anxiety Scale (PRAS-10) [50]). The PRAS measures the frequency and severity of pregnant people’s present concern, worry, or fear about various aspects of their pregnancy and delivery*.* Items are scored on a 4-point Likert scale (1=never, 4=almost all the time), with a possible total score of 4-40, where higher scores indicate greater pregnancy-specific anxiety. The PRAS shows good reliability and internal consistency across diverse samples of pregnant people [21,50,51].

#### Insomnia Symptoms

Insomnia is self-reported using the 7-item Insomnia Severity Index (ISI-7 [52]). The ISI measures the nature, severity, and impact of insomnia symptoms over the last month. Items are scored on a 5-point Likert scale (0=no problem, 4=very severe problem), with a possible total score of 0-28, with higher scores indicating greater insomnia severity. The ISI shows excellent internal consistency and reliably distinguishes between clinical and nonclinical sleep problems [53]. It is also considered reliable, and structurally invariable in pregnant people [54].

#### Safety and Adverse Events

Per the UCSF Human Research Protection Program, an adverse event is defined as any untoward or unfavorable medical occurrence in a human participant, including any abnormal laboratory finding, symptom, or disease, temporally associated with the individual’s participation in the research, whether or not considered related to the individual’s participation in the research. All adverse events will have their relationship to study procedures, including the intervention, assessed by an appropriately trained clinician based on temporal relationship and clinical judgment. Adverse event reporting will be done in keeping with the WCG IRB Policy HRP-071. Specifically, adverse events will be reported within 5 calendar days of principal investigator awareness when the adverse event requires a change to the protocol or consent document. For additional information regarding documentation and definition of adverse events in the THRIVE trial, see Multimedia Appendix 4.

#### Analyses

To examine the efficacy of dCBT (Daylight) on generalized anxiety symptoms (primary outcome) and symptoms of depression, stress, pregnancy-specific anxiety, and insomnia (secondary outcomes) from baseline to 10 weeks post randomization, we will use LMMs. These LMMs will be fit with treatment condition (dCBT and waitlist control group) as the between-group factor, time (baseline, 3, 6, and 10 weeks post randomization) as a within-group factor, and a group-by-time interaction. LMMs maximize data use because they produce unbiased parameter estimates in situations where there are different numbers of observations per record, so long as data are missing at random. A model-based approach will be used to assess the potential impact of data missing not at random on our findings. Pattern mixture models will be used to identify missingness patterns (eg, differential attrition based on randomization group) and to stratify analysis by these patterns as needed [55]. All primary and secondary analyses will be conducted on all randomized participants using an intention-to-treat approach. Sensitivity analyses will also be conducted to test the effects of Daylight among participants who (1) download the app, (2) complete at least 2 modules, and (3) complete all 4 modules, mirroring planned analyses from the original Daylight efficacy trial [56]. Finally, dependent on sample size, exploratory moderation analyses will be conducted to test for differential intervention efficacy among subgroups of racial, ethnic, or sexual and gender minoritize. No interim analyses are planned.

Regarding the assessment of dCBT acceptability, focus groups will be transcribed for qualitative analysis. In line with implementation science frameworks, we will use rapid qualitative techniques for thematic network analysis [57] using NVivo (version 11.4.2; Lumivero) software. Following the identification of codes, the 4 raters will meet to discuss differences and similarities amongst codes to ensure consistency. Codes will be refined and discussed until consensus amongst raters is reached.

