This study is designed to enroll marginalized (Latinx; Black, Indigenous, and people of color; or LGBTQ+ individuals) individuals at a ratio of 2:1. To ensure that randomization is in keeping with our intention of equal representation across groups, we will use a 1:1 allocation ratio with blocked randomization of marginalized people and not. The randomization sequence will be generated by the study biostatistician. The randomization sequence and block sizes will be concealed from all other study team members and participants. Study team members will not be able to influence randomization. Once an eligible participant completes their consent and enrollment survey, unmasked study staff will reveal the allocation assignment and notify participants of their assigned condition. The principal investigator and any staff member involved in data analysis will be blinded to condition assignment. Although we cannot blind participants from condition assignment, allocation will occur after the participant has enrolled to avoid selection bias.

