#### Sample Size

In total, 110 pregnant people with elevated anxiety symptoms will be randomized to one of 2 study arms. Based on a previous study wherein the response to the Daylight tool (by the GAD-7; [34]) at 10 weeks post randomization was normally distributed with a mean of 12.15 (SD 4.73) in the waitlist control, and a mean of 7.90 (SD 4.85) in the dCBT group [31], we expect that a sample of 55 experimental and 55 control participants should detect a true difference in the mean symptoms of experimental and control participants of –2.696 or 2.696 with 80% power. An additional 22 participants will be recruited (ie, a total of 132 enrolled) to account for attrition rates of 17%, the average rate of attrition of marginalized pregnant people enrolled in psychological intervention studies [35]. While we are powered to detect intervention effects at 2 posttreatment time points (6 weeks and 10 weeks following randomization), we do not have pilot data to estimate power at our postpartum time point. Estimates of an effect size in this perinatal pilot are challenging to calculate, as gestational age may vary widely at enrollment (8-27 weeks) resulting in a postpartum assessment that will be up to 36 weeks post treatment for those enrolling at 8 weeks and as early as 15 weeks post treatment for those enrolling at 27 weeks. Thus, treatment effects at the 7-week postpartum time point are exploratory, and we will rely on effect sizes to describe effects as opposed to *P* values.

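### The linear mixed model lets the arms differ freely at baseline, so its week-10 contrast compares change scores and can give up some precision; adjusting for baseline and the randomization stratum costs only wording

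*Protocol article*

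**What the plan says.** In Analyses, the primary and secondary outcomes share one model. Its terms are given in full: "These LMMs will be fit with treatment condition (dCBT and waitlist control group) as the between-group factor", then "time (baseline, 3, 6, and 10 weeks post randomization) as a within-group factor, and a group-by-time interaction". The Results paragraph of the Abstract lists the same terms. Neither place names a baseline covariate, a constraint on the baseline means or a stratification term.

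Under Randomization and Blinding, the article says "we will use a 1:1 allocation ratio with blocked randomization of marginalized people and not", with marginalized participants enrolled at 2:1.

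Under Sample Size, the trial is sized on a between-group difference in 10-week GAD-7 means. The source is an earlier trial with a "mean of 12.15 (SD 4.73) in the waitlist control, and a mean of 7.90 (SD 4.85) in the dCBT group". From this the plan expects that "a sample of 55 experimental and 55 control participants" will "detect a true difference in the mean symptoms of experimental and control participants of –2.696 or 2.696 with 80% power". No baseline correlation enters that calculation.

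**The concern.** Baseline is a level of the time factor, and the model has both a group effect and a group-by-time interaction. The arms therefore keep an unconstrained difference at baseline. The week-10 interaction coefficient is the week-10 difference minus the baseline difference. It subtracts chance baseline imbalance in full, where an adjusted analysis subtracts only the share that predicts the outcome.

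Randomization makes the expected baseline difference zero, so estimating it freely adds noise without removing bias. If the correlation is low enough, the change contrast is even less precise than the plain week-10 comparison used for sizing. Separately, randomization is blocked by marginalized status, and that factor is not among the listed terms. What is at stake is power and interval width, from data the trial collects anyway.

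**Working it through.** **Inputs from the article.** 55 per arm; difference 2.696; 10-week SDs 4.73 and 4.85; stratum mix 2:1; GAD-7 of at least 10 at entry on a scale ending at 21.

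**Assumptions, because the article gives no figure.** Two-sided alpha 0.05; baseline SD (s0) 3.0-3.2; baseline-to-week-10 correlation (rho) 0.3-0.6; the test is the week-10 contrast.

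**Step 1: the plan's own figure.** Pooled SD = sqrt((4.73² + 4.85²)/2) = 4.79. With 55 per arm, a two-sample t-test at 2.696 has 83.3% power. An SD of 5.0 gives 80.0%, so a value near 5.0 seems to have been used. I carry both as the week-10 SD (s1).

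**Step 2: the two contrasts.**
- Change score: V_change = s1² + s0² - 2·rho·s0·s1
- Baseline-adjusted: V_adj = s1²·(1 - rho²)
- Difference: V_change - V_adj = (s0 - rho·s1)², which cannot be negative.

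Example with s1 = 4.79, s0 = 3.0, rho = 0.3: V_change = 22.94 + 9.00 - 8.62 = 23.32. V_adj = 22.94 × 0.91 = 20.88. The reduction is 2.44/23.32 = 10.5%. Power goes from 82.7% to 86.6%.

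**Step 3: the range** (power from the noncentral t, 55 per arm, difference 2.696).

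| s1 | s0 | rho | Variance reduction | Power, change | Power, adjusted |
|---|---|---|---|---|---|
| 4.79 | 3.0 | 0.3 | 10.5% | 82.7% | 86.6% |
| 4.79 | 3.2 | 0.3 | 13.0% | 81.6% | 86.6% |
| 5.0 | 3.0 | 0.3 | 9.0% | 80.0% | 83.6% |
| 5.0 | 3.2 | 0.3 | 11.3% | 79.0% | 83.6% |
| 4.79 | 3.0 | 0.4 | 5.7% | 87.3% | 89.1% |
| 4.79 | 3.2 | 0.4 | 7.9% | 86.5% | 89.1% |
| 5.0 | 3.0 | 0.4 | 4.5% | 84.8% | 86.4% |
| 5.0 | 3.2 | 0.4 | 6.4% | 84.1% | 86.4% |
| 4.79 | 3.0 | 0.5 | 2.1% | 91.7% | 92.2% |
| 4.79 | 3.2 | 0.5 | 3.6% | 91.2% | 92.2% |
| 5.0 | 3.0 | 0.5 | 1.3% | 89.5% | 89.9% |
| 5.0 | 3.2 | 0.5 | 2.5% | 89.1% | 89.9% |

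At rho 0.6 the reduction is under 1% throughout. The change contrast falls below the plain week-10 comparison only when rho < s0/(2·s1), which is about 0.30-0.33 here.

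**Step 4: cross-check with all four visits.** A generalized least squares calculation used 66 randomized per arm, 17% monotone dropout, exchangeable correlation and baseline SD 3.0. Power with a free versus a constrained baseline was 84.1% and 87.3% at rho 0.3, 88.4% and 89.9% at 0.4, and 92.5% and 92.9% at 0.5. This agrees with Step 3.

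**Step 5: secondary outcomes.** These have no entry cutoff. If baseline and follow-up SDs are equal, V_adj/V_change = (1 - rho²)/(2(1 - rho)) = (1 + rho)/2. The saving is (1 - rho)/2, for example 25% at rho 0.5.

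**Step 6: the stratum.** In a 2:1 mix, strata that differ by D points explain R² = D²·(2/9)/s1² of the variance. With s1 = 4.79, D = 1 gives R² = 0.0097 and D = 2 gives 0.0387. Power of a follow-up comparison rises from 83.3% to 83.6% and 84.7%.

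**The case against.** The strongest reply is that nothing here is invalid. A group-by-time model with baseline as a level is widely used and unbiased under missing at random. Leaving out a stratification factor makes inference at most slightly conservative. Power at the earlier trial's difference (12.15 - 7.90 = 4.25 points) is about 99% with the change contrast even at rho 0.3. All of that stands.

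A second reply is that a journal article condenses the full protocol, and covariates are often left to the SAP. That holds for the stratum: its absence from the listed terms does not show that it will be excluded. It does not settle the baseline point, because the article states twice that baseline is an outcome level.

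Three stronger readings are tempting and are not supported:

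- A reader might set baseline and week-10 SDs both at 5.0 and, at rho 0.4, find a 30% variance saving. Entry at 10 or more confines baseline GAD-7 to 10-21. Even a uniform spread over that range has SD 3.45, so an SD of 5.0 would need most participants at the two extremes.
- A reader might argue that the entry cutoff lowers the correlation and so makes the loss more likely. Write the excess as s0²·(1 - b)², with slope b = rho·s1/s0. If the regression is linear, restricting baseline leaves b and the residual variance unchanged and shrinks s0. Truncation then reduces the loss.
- A reader might say that omitting the stratum inflates the standard error of the planned contrast. A stratum effect that is constant over time cancels from a change score, so the gain in Step 6 applies to a follow-up comparison.

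**Conclusion.** The point holds as a modest matter of efficiency. As written, the week-10 contrast is a difference in change scores, and its variance exceeds that of the adjusted contrast by (s0 - rho·s1)². The direction needs no assumption, apart from about one degree of freedom spent on a covariate. The size does: under the assumptions above, the GAD-7 gain is 3.5-5 power points at correlation 0.3, about 2 at 0.4, under 1 at 0.5 and essentially none near 0.6. The documents do not say where in that range this trial lies, nor whether the test is the week-10 contrast or the joint interaction. Secondary outcomes may gain more. The stratum is worth about 0-1.5 power points for differences up to 2 points; the main reason to include it is consistency with the blocked randomization. It should not be inferred that the planned analysis is biased or that the trial is underpowered because of it.

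**What to change.** Reword the model in Analyses, and the matching sentence in the Abstract, in one of two ways:

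1. Keep baseline as an outcome level but constrain both arms to a common baseline mean. This keeps every randomized participant in the likelihood, which suits the stated intention-to-treat analysis.
2. Model weeks 3, 6 and 10 as outcomes, with baseline score by time as a covariate. This avoids treating a GAD-7 score cut off at 10 as a normal outcome, but drops participants who have no follow-up score.

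In either form, add the randomization stratum (marginalized or not) as a fixed effect, and use the same model for the secondary outcomes.

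The cost is analysis wording only: no extra data, visits or participants. The change should be recorded before analysis begins, while the principal investigator and analysis staff remain blinded as planned.

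### The three app-use sensitivity analyses select participants on behaviour after randomization that controls cannot show before week 10, so they are not randomized comparisons and do not test the ITT result

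*Protocol article*

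**What the plan says.** The Analyses section sets the main population correctly: "All primary and secondary analyses will be conducted on all randomized participants using an intention-to-treat approach". Efficacy is assessed "from baseline to 10 weeks post randomization, we will use LMMs", with treatment group, time (baseline, 3, 6 and 10 weeks) and their interaction.

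It then adds three analyses under a sensitivity label, to "test the effects of Daylight among participants who (1) download the app, (2) complete at least 2 modules, and (3) complete all 4 modules". The reason given is that the original Daylight efficacy trial planned the same. The article does not say how controls enter these analyses.

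The Waitlist Control section fixes when controls can use the app: "The waitlist control group participants will get complimentary access to the Daylight program after completing the 10-week follow-up survey". Randomization and Blinding agrees, with control access at 10 weeks.

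The Daylight section shows that use is the participant's own choice ("Daylight is designed to be self-paced, with the app encouraging users to practice techniques") and that the investigators expect incomplete use; reminders are there to "encourage daily use and intervention adherence, a prominent challenge in digital interventions".

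**The concern.** Each of the three populations is defined by something participants do after allocation. Within the baseline-to-10-week window only the dCBT arm can do it through the trial, so the criteria cannot be applied alike to both arms.

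People who download the app and finish modules may have had a different course without it. If so, the comparison mixes the effect of Daylight with that difference. The mixed models and pattern-mixture models do not help. They deal with outcomes that are missing, whereas here participants are excluded by design because of later behaviour.

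The label matters too. A sensitivity analysis keeps the question and varies an assumption behind the answer. These analyses change the population and the estimand, so agreement with the ITT estimate would not support it and disagreement would not undermine it. What is at stake is how three user-only estimates, described as effects of Daylight, are read beside the ITT result.

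**Working it through.** **1. Two ways to apply the criteria**

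| Reading | dCBT arm | Waitlist arm, to week 10 | Result |
|---|---|---|---|
| Criteria applied to the dCBT arm only | Users only | Everyone: would-be users and would-be non-users | Not a randomized comparison |
| Criteria applied to both arms | Users only | Nobody qualifies | Uncontrolled pre-post change |

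**2. Bias under the first reading**

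Let p be the share of the dCBT arm meeting the criterion. By randomization, the same share of controls would have met it had they been offered the app. Let m_u and m_n be the mean untreated change from baseline in would-be users and would-be non-users.

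- Mean change in all controls = p·m_u + (1 − p)·m_n.
- Mean change in dCBT users = m_u + effect in users.
- Difference = effect in users + (1 − p)·(m_u − m_n).

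The last term is the bias. The planned contrast is a group-by-time interaction with baseline as one of the time points. A gap already present at baseline therefore cancels: if the user/non-user gap is g0 at baseline and g10 untreated at week 10, the bias is (1 − p)·(g10 − g0).

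**3. Inputs**

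- SD: Sample Size gives 4.73 and 4.85, so the pooled value is √[(4.73² + 4.85²)/2] = 4.79.
- Yardstick: the stated detectable difference of 2.696 points with 55 per arm and 80% power. Assuming two-sided α = 0.05 and SD 4.79, the normal formula gives (1.960 + 0.842) × 4.79 × √(2/55) = 2.56 (2.58 with the t distribution). A t-test with SD 5.0 gives 2.695. The stated figure is thus slightly conservative for its quoted SDs. That is a separate matter; 2.696 only sets a scale here.
- p, g0 and g10: not in the article. Assumed p = 0.3 to 0.7 and g10 = 0.2 to 0.5 SD.

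**4. Illustration with equal baselines (g0 = 0)**

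| p | g10 (SD) | (1 − p) × g10 × 4.79 | Share of 2.696 |
|---|---|---|---|
| 0.7 | 0.2 | 0.3 × 0.2 × 4.79 = 0.29 | 11% |
| 0.5 | 0.3 | 0.5 × 0.3 × 4.79 = 0.72 | 27% |
| 0.3 | 0.5 | 0.7 × 0.5 × 4.79 = 1.68 | 62% |

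**5. How far this depends on the assumptions**

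- Part of the gap present at baseline: with p = 0.3, g10 = 0.5 and g0 = 0.3, the bias is 0.7 × 0.2 × 4.79 = 0.67, not 1.68.
- Use unrelated to prognosis: the bias is 0.
- Early improvers stop using the app: the sign can reverse, against Daylight.

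**6. Simulation check (no true effect, 55 per arm, 20,000 trials per setting)**

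The dCBT arm was cut to the fraction f most inclined to use the app, with that inclination correlated ρ with a lower week-10 score. At ρ = 0 the bias was about 0 and the two-sided error rate 5%. At f = 0.8, ρ = 0.2 they were −0.34 points and 6.4%; at f = 0.4, ρ = 0.3, −1.39 points and 20.4%. This model also has no baseline term. It confirms the mechanism, not the size under the planned model.

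**7. Complier-average effect**

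When only the dCBT arm can fail to take up its assigned treatment, the complier-average effect is ITT/p. It is 0 when the ITT effect is 0. For an ITT effect of −2.696 it is −3.85 at p = 0.7, −5.39 at p = 0.5 and −8.99 at p = 0.3.

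**The case against.** **The comparator is not stated.** This stands as a limit. A reader might infer that the article commits to dropping non-users and keeping every control. It does not say so. An effect among downloaders could even describe a complier-average target, and the method may be set out in the earlier trial's plan or in the full clinical protocol, neither of which is shown. But the article does fix the three populations and the sensitivity label, and neither way of applying the criteria gives a randomized comparison.

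**The size is assumed, and the planned model removes stable differences.** This also stands. Only the SD comes from the article. The 0.3 to 1.7 range needs equal baseline scores in users and non-users.

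**A complier-average effect has faults of its own.** This stands for the module thresholds. At 2 or 4 modules it assumes that lesser use does nothing, which is doubtful. It also rises mechanically as p falls, so it would create a gradient across thresholds by construction. For downloading, the assumption that being offered the app without downloading it has no effect is plausible. The test will largely repeat the ITT test; what it adds is an estimate for downloaders.

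**No conclusion hangs on these analyses.** Correct for the primary and secondary outcomes, which stay on all randomized participants. That limits the weight of the point but does not make the label right.

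**Conclusion.** The point holds as a flaw in supplementary analyses. The three app-use comparisons, as described, are not protected by randomization, target a different estimand, and do not test the robustness of the ITT result. The primary ITT conclusion is unaffected.

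The size cannot be read from the article. The 0.3 to 1.7 GAD-7 points rest on assumed p of 0.3 to 0.7, an assumed untreated difference of 0.2 to 0.5 SD (SD 4.79) and equal baseline scores. The bias is smaller if part of the difference is already there at baseline, and zero if use is unrelated to prognosis.

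Two stronger readings are not supported. A reader might infer that the bias must favour Daylight; the article gives no basis for a direction. A reader might also expect a spurious dose-response across the three thresholds. That is possible, but it requires the user/non-user difference not to shrink as the criterion tightens, and nothing in the article shows this.

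**What to change.** - Relabel the three analyses as supplementary and state the estimand of each.
- For downloading the app, replace the subset comparison with a complier-average causal effect on all randomized participants. Use randomization as the instrument and adjust for baseline GAD-7 and the randomization stratum. Handle missing outcomes consistently with the primary model, since 17% attrition is expected.
- State the assumption that being offered the app without downloading it has no effect.
- Report participants completing at least 2 modules, or all 4, descriptively and without efficacy claims.

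The cost is wider intervals than the naive subsets would show and modest extra analysis work. No new data are needed, because the app already records engagement. The article reports 24 participants randomized by March 2025 and results expected in May 2026, so on its own timeline the change could be made before analysis.
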